**Figure 3 F3:**
[figure not shown]
**Randomization Implementation Process**.

### Interventions for each group

Participants assigned to the SMATH^® ^therapy group (A arm) will have 14 treatment sessions of 45 minutes over 4 weeks starting at T2. The treatment module is associated with a dedicated educational booklet for each patient that provides general and behavioral indications for preventing LBP. In this clinical study, the educational booklet will be delivered to all enrolled participants to help them correct their lifestyle during and after the intervention period. In this dedicated booklet, different sections explain to the participants spine anatomy, LBP, LBP prevention, advantages of physical activity, suggestions for positions for walking, sleeping, and to keep weight under control, and exercises to prevent LBP.

During the first and second week (from T2 to T3), 4 sessions will be done per week, whereas 3 sessions per week will be planned for the third and fourth week (from T3 to T4). The SMATH^® ^system will be set-up with treatment variables (warm-up time, automatic treatment program, active element temperature, infrared insertion) conforming to the scheduled treatment data sheet delivered to the technician after randomization. Sham therapy will be implemented using a dedicated SMATH^® ^device. This medical device, which was conceived and manufactured exclusively for this clinical study, has the same external look and design of the SMATH^® ^device. The active principles (thermomechanic and infrared energy release) have been fully blocked in the sham device, but the participants' perceptions will be more or less the same (warm, vibration, noise). The engineering department has made important efforts to create a device with the appearance of the active machine, inducing feelings similar to those of the real device [19]. This effect has been obtained by applying some technical solutions without releasing any active energy. Thermal perception is generated using special lamps with different wavelengths than the real SMATH^® ^device with 90% less thermal power (just to induce the feeling of heat). Infrared emission has been removed, as well as the active rollers that release mechanical energy to the back and legs, replaced by an inert, flat wood plate. The sham device will be set-up with the same treatment variables as the SMATH^® ^device. The noise and vibration generated by the sham device will be the same as that of the SMATH^® ^system because the devices have the same mechanical configuration, including the same motor and transmission equipment, operating in the same mode. Despite this similarity, a therapeutic placebo effect could be introduced by the sham device. This risk has been considered and accepted as a natural risk of the RCT with a sham control.

Participants assigned to the sham therapy arm will receive the same treatment module scheduled for the active SMATH^® ^arm (14 sessions in four weeks from T2 to T4). The participants in the sham arm will also receive the educational booklet. The SMATH^® ^and sham devices are located inside two different therapy boxes and treatment will be given at separate times to prevent contact between participants in the different treatment arms. The operators managing treatments will be the same for the SMATH^® ^and sham devices, and they have been trained to answer the participants' questions about the procedures. The same operators will also be trained and educated in keeping participants in the study, avoiding an increased drop-out rate. The main features of the SMATH^® ^system and sham version are presented in Figures 4 and 5, respectively.

**Figure 4 F4:**
[figure not shown]
**The SMATH^® ^System**.

**Figure 5 F5:**
[figure not shown]
**The SMATH^® ^sham version**.

## Discussion

### Outcomes

This clinical study was designed to include the following general outcome measures: pain, overall improvement, back-specific functional status, well being (quality of life), and disability. The questionnaires that will be used to collect data from the participants are: visual analog scale (VAS) for pain [12], Roland Morris Disability Questionnaire (RMDQ) for effectiveness, specifically back-specific disability [12], and Euro Qol-5D questionnaire (EQ-5D) for quality of life, which is one of the most used and suitable questionnaires for QALY calculation [5]. These questionnaires were chosen by considering the major systematic reviews regarding physical and rehabilitory interventions for sub-acute and chronic non-specific LBP [2,4,9,10,12,15]. Participants will complete the VAS at T2, T3, T4, TF1, TF2, TF3, TF4, and TF5; RMDQ at T1, T2, T3, T4, TF1, TF2, TF3, TF4, and TF5; and EQ-5D at T2, T4, TF1, TF2, and TF5.

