
## Trial Rationale

SMATH^® ^is a new medical device that combines basic principles of mechanical massage, thermotherapy, acupressure, infrared therapy, and moxibustion. SMATH^® ^is included in the "conservative treatments" category [13]. This device is capable of releasing modulated and controlled thermomechanic energy on the patient following a programmable and fully reproducible automatic treatment program selected by the operator. Energy (thermomechanic and infrared) is released at the same time under the spine and legs of the patient. We think this system provides a true automatic multidisciplinary treatment for patients with sub-acute and chronic LBP. The SMATH^® ^system should theoretically be capable of combining the single clinical benefits of massage, thermotherapy, infrared, and acupressure, removing the dependency on operator capability, though obviously missing some elements of human touch, and providing maximum automaticity and reproducibility and producing a real clinical added value for patients. The literature involving different reviews show that little clinical evidence exists on the use of these endorsed therapies on their own. In particular, there is little evidence for massage performed by hands or a mechanical device, or and for superficial heat release [12]. No evidence is available for thermotherapy [13], or for moxibustion, infrared therapy, and acupressure. On the other hand, moderate evidence indicates the effectiveness of multidisciplinary treatment compared to other kinds of active treatment in regards to pain intensity at short-term follow-up [12]. The SMATH^® ^system was developed in an attempt to create an effectiveness advantage by combining different basic theoretical principles. The first clinical results, from the safety clinical study involving 46 patients inside the process to obtain the European Conformity (CE) mark for SMATH^®^, showed the following: RMDQ average score of 10.96 (sd = 3.04; p < 0.05) at baseline and 3.21 (sd = 2.99; p < 0.05) after 3 months, and the average quality adjusted life year (QALY) was 0.46 (sd = 0.13; p < 0.05) at baseline and 0.81 (sd = 0.12; p < 0.05) after 3 months. These data have not been published because they were not suitable for publication and represented the results obtained by one clinical study in which the primary outcome was the demonstration of clinical safety. The internal clinical report concerning this study has been delivered to the notified body in charge of the CE mark process. The SMATH^® ^system obtained the CE mark on 20 December 2010. The current RCT was designed to investigate and test the SMATH^® ^system for use in LBP therapy.

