## Methods

### Design

This is a double-blinded, sham-controlled, randomized, single-center short term clinical trial involving 72 participants. Thirty-six participants will be treated with SMATH^® ^therapy and compared to 36 participants treated with sham therapy (same medical device without active principles). All participants are patients with non-specific sub-acute and chronic LBP, aged 18 to 70 years. Exclusion criteria verification will be done at baseline (T1) with the identification of eligible participants. One week after T1 (T2), eligible participants who have signed informed consent and satisfy the inclusion criteria will be randomized into either the SMATH^® ^or sham groups. Participants who are not randomized will be submitted to the most suitable therapy by the investigators and sent to TF1 to enter in the observational follow-up. Randomized participants will attend clinic visits at T2 (one week after T1), T3 (two weeks after T2) and T4 (two weeks after T3). The design of the clinical trial is depicted in Figure 1. At T4, treatments will be complete and all participants can continue the most suitable therapy, as indicated by the investigators, and enter the long-term observational follow-up phase, which will last 11 months. All participants will be followed starting at TF1 (same time as T4,) for 11 months and will attend clinic visits at 1 month (TF2), 4 months (TF3), 7 months (TF4), and 11 months (TF5) after TF1. The design of the observational follow-up period is depicted in Figure 2.

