### Secondary outcomes

The secondary outcomes of the trial are: 1) Effectiveness of SMATH^® ^determined by evaluating self perceived physical function comparing RMDQ scores between end of treatment and baseline. 2) Pain perception change from baseline (T2) to end-treatment (T4), evaluated by VAS scores. 3) Quality of life at different steps of the study (T2 and T4), evaluated by EQ-5D scores (QALY). 4) Verified general feasibility of the medical device compared to sham therapy in terms of methodology, sample size, and drop-out rate, among other measures, to constitute a real pilot study and act as a possible reference for future generations of RCTs involving the medical device, conforming to the evidence-based medicine (EBM) criteria for LBP therapy [13] according to the CONSORT statement based on new methodological evidence and to the International Placebo Symposium Working Group recommendations [19].

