### Observational follow-up and duration of the study

Observational follow-up will start at TF1 (T4) and cover 11 months. During this period, all of the participants will come to the treatment centre to attend clinic visits one month after TF1 (TF2), 3 months after TF2 (TF3), 3 months after TF3 (TF4), and 4 months after TF4 (TF5). Figure 2 shows the design of the observational follow-up period. The estimated study duration for enrollment, execution and observational follow-up will be 18 months.

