### Assessment of outcomes

Four steps of participant examination are planned in this RCT (T1, T2, T3, and T4); during which, general clinical data will be collected about the persistence of LBP symptoms, previous treatment, morphological data, patient activity, blood chemistry tests, anamnesis, and eventual clinically important imaging investigations that were recently done. The effectiveness of SMATH^® ^versus sham will be determined by evaluating self-perceived physical function with RMDQ scores at T4. The secondary outcome of SMATH^® ^therapy effectiveness will be determined by evaluating improvements in patients' motion functionality between T2 and T4 using RMDQ scores. The evolution of pain perception during the study will be measured by VAS scores submitted by the participants at T2, T3, and T4. Quality of life for participants will be estimated by the comparing the EQ-5D questionnaires submitted at the beginning and end of treatment (T2 and T4). During the observational follow-up period all participants will be examined at TF1, TF2, TF3, TF4, and TF5 for general patient status: anamnesis, blood pressure, heart rate in beats per minute, and morphological variables (height, weight, Body Mass Index [BMI]). The RMDQ and VAS questionnaires will be given on the participants at TF1, TF2, TF3, TF4, and TF5, and EQ-5D will be given at TF1, TF2, and TF5. All of the data collected during the study and follow-up will be reported to the CRF.

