### Statistics and quality

The accuracy and completeness of the collected and registered data will be checked daily by clinical investigators to provide a suitable level of quality for the study. The external monitor will be responsible for arranging random periodic tests of quality throughout the study. In particular, controls will involve the quality and completeness of the CRFs, the treatment execution modalities, the drop-out rate, and correct respect of enrollment criteria application. Data analysis will be conducted using IBMSPSS 19 [21,22]. The morphological and clinical status of participants will be analyzed statistically. Motion functionality, level of pain perception, and quality of life will be evaluated through statistical analysis of the questionnaire scores. Short-term results will be evaluated to elaborate VAS and RMDQ scores, and medium and long-term results will be evaluated by EQ-5D scores, which will also be used to calculate the QALY and incremental cost effectiveness ratio (ICER) index [5,22], which is the most used and suitable index for analyzing the cost/effectiveness of PRM therapies [5]. Pain perception measured by VAS in the different phases and its severity analysis will be evaluated by analysis of variance using SPSS 19. Event incidence (SMATH^® ^versus sham) will be estimated using Kaplan-Meier curves, which will be compared using the log-rank test. Multivariable analysis will be performed using the Cox model.

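### EQ-5D carries the medium- and long-term results, the QALY and the ICER, but is not collected at TF3 or TF4, so the QALY and ICER may be materially biased

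*Protocol article*

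**What the plan says.** The Statistics and quality section of the protocol article gives the short-term results to VAS and RMDQ. For the later period it states that "medium and long-term results will be evaluated by EQ-5D scores", and it uses the same scores for the QALY and the ICER.

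The Outcomes section lists "EQ-5D at T2, T4, TF1, TF2, and TF5". The Assessment of outcomes section agrees: "EQ-5D will be given at TF1, TF2, and TF5". The same section says of the other two instruments: "The RMDQ and VAS questionnaires will be given on the participants at TF1, TF2, TF3, TF4, and TF5".

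On timing, the Design section says participants "will attend clinic visits at 1 month (TF2), 4 months (TF3), 7 months (TF4), and 11 months (TF5) after TF1". The follow-up section adds "Observational follow-up will start at TF1 (T4) and cover 11 months", so TF1 and T4 are one time point.

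On terminology, the third secondary outcome is quality of life at T2 and T4, "evaluated by EQ-5D scores (QALY", with QALY in brackets as if it were another name for the score. The Trial Rationale reports of an earlier safety study that "the average quality adjusted life year (QALY) was 0.46" at baseline and 0.81 after 3 months.

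**The concern.** EQ-5D is the only one of the three questionnaires not given at the two middle follow-up visits, yet it is the one chosen for results beyond the short term and for the health-economic analysis. Because TF1 equals T4, the five listed EQ-5D assessments are four distinct times, and only two of them fall after the end of treatment: 1 month and 11 months. An analysis plan can choose how to bridge that gap, but it cannot recover data that were not collected.

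The Design section opens therapy to whatever the investigators judge suitable after T4, so there is no reason to presume that the difference between arms moves in a straight line over those 10 months. The Trial Rationale says the results will inform a health technology assessment already under way, so an error in the QALY difference would pass into a policy document.

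The second matter is the label. A QALY is utility accumulated over time. A score at a single visit is a utility, and none has accumulated at baseline. If the label were taken literally in the analysis, score differences would enter the ICER as QALYs.

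**Working it through.** **The document's own QALY figures.** The only ones are 0.46 at baseline and 0.81 after 3 months, in the safety study. With utility at most 1, at most 3/12 = 0.25 QALY can accrue in 3 months, and 0 at baseline. Neither figure can be reproduced as a QALY; both can only be utilities at a visit. A linear rise from 0.46 to 0.81 over 3 months is a gain of 0.35 × 0.25 / 2 = 0.044 QALY over staying at 0.46; an immediate rise gives 0.35 × 0.25 = 0.0875.

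**Inputs from the article.** T2 to T4 is 4 weeks = 28/30.4375 = 0.92 months. TF2, TF3, TF4 and TF5 are 1, 4, 7 and 11 months after T4. The horizon from T2 to TF5 is 11.92 months.

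**Share resting on one line.** TF2 to TF5 is 11 − 1 = 10 months, and 10/11.92 = 84% of the horizon.

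**Assumptions.** The documents give no utility difference. I take 0 between arms at T2 and 0.10 at T4 and TF2, and vary the path after that. QALY difference = sum over intervals of (length in years) × (mean of the differences at its two ends).

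Common to every path, T2 to TF2: 0.0767 × 0.05 + (1/12) × 0.10 = 0.0038 + 0.0083 = 0.0122.

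After TF2, with the scheduled visits only and a difference of 0 at TF5: (10/12) × 0.05 = 0.0417. Total 0.0538.

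After TF2, with TF3 and TF4 available:
- Gone by TF3: (3/12) × 0.05 = 0.0125. Total 0.0247.
- Held to TF4, gone by TF5: (6/12) × 0.10 + (4/12) × 0.05 = 0.0667. Total 0.0788.
- Partial early loss (0.05 at TF3, 0.02 at TF4, 0 at TF5): 0.25 × 0.075 + 0.25 × 0.035 + (4/12) × 0.01 = 0.0308. Total 0.0430.
- Linear fade (0.07, 0.04, 0): 0.0417. Total 0.0538.
- Constant 0.10 to TF5: (10/12) × 0.10 = 0.0833. Total 0.0955, by either schedule.

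| Path after TF2 | With TF3 and TF4 | As scheduled | Error |
|---|---|---|---|
| Gone by TF3 | 0.025 | 0.054 | +118% |
| Partial early loss | 0.043 | 0.054 | +25% |
| Linear fade to TF5 | 0.054 | 0.054 | 0 |
| Constant | 0.096 | 0.096 | 0 |
| Held to TF4, then lost | 0.079 | 0.054 | −32% |

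**Cross-check.** A departure of the true difference from the TF2–TF5 line has weight (3 + 3)/2/12 = 0.25 year at TF3 and (3 + 4)/2/12 = 0.292 year at TF4. For loss by TF3 the departures are −0.07 and −0.04: 0.25 × 0.07 + 0.292 × 0.04 = 0.029 = 0.0538 − 0.0247, rounded. The two methods agree.

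**Effect on the ICER.** The QALY difference is the denominator. For a given cost difference, the ICER would be 0.0247/0.0538 = 0.46 of its proper value in the first row and 0.0788/0.0538 = 1.46 times it in the last.

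**The case against.** A reader might infer that the cost-effectiveness result must come out wrong. The documents do not support that. An area under the curve can be formed from T2, T4, TF2 and TF5, and it has no error if the arm difference is constant or linear after TF2. Error appears only under non-linear paths, in either direction, and its size rests on an assumed difference of 0.10. Adding TF3 and TF4 shortens the interpolated segments but does not abolish interpolation. All this stands, and it limits the finding to possible bias.

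A reader might also infer that the trial will use scores as QALYs and so overstate the gain 4 to 8 times (0.35 against 0.0875 to 0.044). That is not shown either. The Outcomes and the Statistics and quality sections describe EQ-5D as an input from which a QALY is calculated, and the formula may be in the full protocol or analysis plan. The 0.46 and 0.81 are background from another study with no comparator figures given. What stands is that the label in the third secondary outcome is wrong as written.

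The article never defines medium term, so TF2 might be meant. That would weaken a claim that no medium-term measurement exists, but not the point about the QALY and ICER, which need the whole course to TF5.

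Finally, open therapy after T4 limits what an 11-month ICER can attribute to the device, whatever the number of questionnaires, and the ICER is not itself a listed secondary outcome. Both are true. They keep the point secondary but do not justify a schedule that is thinnest for the instrument given the longest task.

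**Conclusion.** The point holds as a mismatch between the EQ-5D schedule and the role assigned to EQ-5D. Two sections agree on the schedule, so it is a stated choice and not a slip of one passage. About 84% of the QALY horizon depends on a straight line that the data cannot test. On an assumed difference of 0.10 at T4 and TF2, the error in the T2–TF5 QALY difference ranges from −32% to +118% over the paths tried, with zero error for constant or linear change. The QALY and ICER may therefore be materially biased; the documents do not show that they will be.

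The use of QALY for a score at one visit is a definite error of wording in the third secondary outcome and in the background figures. Whether it would affect the ICER cannot be settled from the article.

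The primary outcome (RMDQ at T4), the sample size and the error rates are untouched.

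**What to change.** Add EQ-5D at TF3 and TF4 in the Outcomes and Assessment of outcomes sections. Both visits are already scheduled and already include two questionnaires. The cost is 2 × 72 = 144 short forms for the randomised participants, more if the non-randomised participants who enter follow-up also complete it, with a minor added burden on respondents. If the visits cannot be added to, state that the QALY depends on linear interpolation from 1 to 11 months and report that limit with the ICER.

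In the third secondary outcome, replace the bracketed QALY wording with *EQ-5D utility*, and keep the term QALY for utility accumulated over time. This costs only an edit.

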### Primary outcome

The primary outcome of the trial is represented by the clinical effectiveness of the SMATH^® ^system versus sham therapy after 4 weeks of treatment in patients with sub-acute and chronic non-specific LBP, determined by evaluating self perceived physical function with RMDQ scores. The status of physical function in participants treated with SMATH^® ^interventions will be compared with the status achieved in participants in the sham control arm at the end of treatment (T4) [12].

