### Eligibility

Subjects with sub-acute and chronic non-specific LBP diagnosed according to generally accepted scientific criteria [13] were enrolled. Inclusion criteria were as follows: aged between 18 and 70 years, ability to sign informed consent, ability to complete the study, ability to complete the questionnaires, RMDQ score ≥ 4 at T2 [20], and negative answers on all exclusion questions at T1. The rationale for the inclusion criteria is provided in Table 1.

**Table 1 T1:** Rationale for Inclusion Criteria

Inclusion criteria	Rationale
Age between 18 and 70 years	This age interval was chosen in accordance with actual main reviews in PRM [2,10,12]

Ability to sign informed consent	Mandatory for participant inclusion in clinical studies (Helsinki Declaration article 22)

Ability to complete the study	To prevent drop-outs

Ability to complete the questionnaire	Mandatory for accurate data collection

RMDQ score ≥ 4 at T2	From the literature [20]

Negative answers for all exclusion criteria	This check performed at T2 confirms that the exclusion evaluation was performed at T1.

Exclusion criteria were as follows: pregnancy (real or suspected) or breast-feeding; receiving physical therapy treatments in the 15 days preceding T1; treatment with cortisone in the month preceding T1, implanted with pacemaker or implantable cardioverter defibrillators (ICD) or, more generally, a user of active implantable devices; use of medullar stimulators and infusion pumps; recent or ongoing deep venous thrombosis (DVT); use of spine stabilization devices; serious osteoporosis associated with bone fracture risk, including soft or acutely infected bone tissues; acute cardiovascular disease; neoplastic disease; systemic rheumatic disease; or traumatic spinal episodes in the 3 months preceding T1. The rationale for the exclusion criteria is provided in Table 2.

**Table 2 T2:** Rationale for exclusion criteria

Exclusion criteria	Rationale
Pregnancy (real or suspected) and breast-feeding	These patients have a risk of some alteration due to the mechanical and thermal energy release

Subjects who received physical therapy treatments in the 15 days preceding T1	These treatments could influence the results of the study

Subjects treated with cortisone in the month preceding T1	This treatment could influence the results of the study

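### The primary contrast is defined as RMDQ status at T4 with no baseline term, although a pre-treatment RMDQ at T2 is collected: precision is given up and part of any chance baseline gap stays in the estimate

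*Protocol article*

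**What the plan says.** The primary contrast is described in the same way in the Abstract, under Primary outcome and under Assessment of outcomes. Under Primary outcome, physical function in the SMATH arm "will be compared with the status achieved in participants in the sham control arm at the end of treatment (T4"). Under Assessment of outcomes, effectiveness against sham "will be determined by evaluating self-perceived physical function with RMDQ scores at T4".

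Baseline RMDQ appears in three other places:

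- The Outcomes section schedules the questionnaire before treatment as well as after: "RMDQ at T1, T2, T3, T4, TF1, TF2, TF3, TF4, and TF5".
- The Eligibility section uses the second pre-treatment score as an entry threshold, "RMDQ score ≥ 4 at T2", with no upper limit stated.
- Under Secondary outcomes, the first item judges SMATH by "comparing RMDQ scores between end of treatment and baseline". Assessment of outcomes restates it as "evaluating improvements in patients' motion functionality between T2 and T4 using RMDQ scores". Neither passage says whether this change is compared between arms.

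The Statistics and quality section says of the questionnaires: "Motion functionality, level of pain perception, and quality of life will be evaluated through statistical analysis of the questionnaire scores". It names analysis of variance for VAS, Kaplan-Meier curves with a log-rank test for event incidence, and a Cox model as the only multivariable method. It names no test or model for RMDQ. The Randomization section calls the sequence stratified but names no stratification factor.

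**The concern.** The article describes two RMDQ analyses: end status between arms, and end status against baseline. It does not describe the one that combines them, a between-arm comparison at T4 that takes account of where each participant started.

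Two things are at stake if the primary contrast is carried out as described. The confidence interval is wider than the collected data require. In addition, a chance difference in starting disability, which no named stratification factor guards against, is partly carried into the estimated effect. Both matter more in a trial of 72 people than in a large one. Fixing the covariate in advance would also prevent a later choice among status, change and adjusted results.

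**Working it through.** **The plan's own figure.** The Sample size calculation section uses success probabilities of 0.50 and 0.10, alpha 0.05 and power 0.90. With a two-sided test, pooled variance under the null and no continuity correction:

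n = [1.96·√(2·0.3·0.7) + 1.2816·√(0.5·0.5 + 0.1·0.9)]² / 0.4² = (1.270 + 0.747)² / 0.16 = 25.4, so 26 per arm.

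The article's drop-out factor gives 26 / 0.85² = 35.99, so 36 per arm and 72 in total. Both figures are reproduced. No RMDQ mean, SD or correlation enters them, so adjusting the RMDQ comparison changes neither.

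**Inputs for the present point.**

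- 36 per arm, from the Sample size calculation section.
- RMDQ SD of 3.04 at baseline and 2.99 at 3 months, from the 46-patient safety study in the Trial Rationale section. Using about 3.0 as the SD at T4 is an assumption: that study reports 3 months, not 4 weeks, and the article mentions no sham arm in it.
- Correlation r between T2 and T4 RMDQ: not given. A range of 0.3 to 0.7 is assumed.

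**Precision.** With one baseline covariate, the variance of the arm difference is multiplied by 1 − r². The unadjusted standard error at T4 is 3.0·√(2/36) = 0.707 points. The adjusted standard error is 0.707·√(1 − r²), and the 95% half-width is 1.96 times that. The equivalent unadjusted trial size is 72/(1 − r²). For comparison, a between-arm analysis of change scores would multiply the unadjusted T4 variance by 2(1 − r) if the SDs are equal.

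| r | Variance ratio 1 − r² | Reduction | SE (points) | 95% half-width | Equivalent unadjusted N | Change-score ratio 2(1 − r) |
|---|---|---|---|---|---|---|
| none | 1 | – | 0.71 | 1.39 | 72 | – |
| 0.3 | 0.91 | 9% | 0.67 | 1.32 | 79 | 1.4 |
| 0.5 | 0.75 | 25% | 0.61 | 1.20 | 96 | 1.0 |
| 0.7 | 0.51 | 49% | 0.50 | 0.99 | 141 | 0.6 |

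Allowing for estimation of the slope at this sample size moves the ratios only to about 0.92, 0.76 and 0.52. The last column shows that the secondary change outcome is no substitute, even if it is compared between arms. It is less precise than ANCOVA at every r shown, and at r = 0.3 it is less precise than the unadjusted T4 comparison.

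**Chance baseline gap.** The standard error of the difference in baseline means is 3.04·√(2/36) = 0.717 points. P(|gap| > 1) = 2·[1 − Φ(1/0.717)] = 0.163, about 16%. The 95% range is ±1.96·0.717 = ±1.40 points.

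**How much of it reaches the estimate.** The expected shift in the unadjusted T4 difference is r·(SD at T4 / SD at T2)·gap, with 2.99/3.04 close to 1. A 1-point gap therefore shifts the result by about 0.3, 0.5 or 0.7 points. A 1.40-point gap shifts it by about 0.41, 0.69 or 0.97 points.

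**Conditional error rate.** Given a baseline gap of k standard errors, the type I error of the unadjusted test is 1 − Φ[(1.96 − rk)/√(1 − r²)] + Φ[(−1.96 − rk)/√(1 − r²)]. At k = 1.96 this is about 8%, 13% or 20% for r = 0.3, 0.5 or 0.7. At an ordinary gap of k = 1 it is 5.0%, 4.8% or 3.9%. Averaged over all randomisations it is 5%.

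**The case against.** The strongest reply is that the article names an endpoint and a contrast, not a model. RMDQ at T4 compared between arms is exactly the response variable of an ANCOVA on T2, so the quoted sentences do not exclude adjustment. Covariates are often left to an analysis plan, and that plan is not shown. This stands as far as it goes: a reader might infer that the article prescribes a raw-score test and discards baseline, and the documents do not support that. No passage says that the T4 comparison is unadjusted, and T2 RMDQ is used for eligibility and for a secondary outcome.

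A reader might also infer that an unadjusted result would be biased or invalid, or that a baseline gap passes in full into the effect. Neither follows. Randomisation keeps the unadjusted comparison unbiased on average with a 5% error rate, and only about r times the gap carries over.

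The size of the gain is also uncertain. The article supplies no correlation, and at r = 0.3 the gain is small. The sample size rests on proportions, so detectable RMDQ differences are not a design quantity here. If the primary analysis were of the success proportion instead, the linear-model figures would not apply as given.

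What remains is that the article states the primary contrast three times without baseline, assigns baseline to a different outcome, and names methods for VAS and event incidence but none for its primary RMDQ comparison. As described, nothing in it leads to an adjusted between-arm result.

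**Conclusion.** The point holds as one of efficiency and conditional balance, not validity. The primary contrast is defined as T4 status, and the article nowhere provides a baseline-adjusted comparison between arms. If the contrast is carried out without adjustment, about 9%, 25% or 49% of the residual variance is left in that could be removed, for r of 0.3, 0.5 or 0.7. There is also about a 16% chance of a baseline gap above 1 point, of which roughly the fraction r would enter the T4 difference.

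These figures assume that r lies in that range, that the SDs at T2 and T4 are both near 3.0 as in the earlier safety study, that the relation is linear, and that 36 per arm are analysed. Fewer completers would widen every interval, and the variance ratios would stay almost the same. It does not follow that the trial is too small: 72 participants and the stated 90% power were derived from success proportions and are untouched by this point.

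**What to change.** Keep the T4 endpoint and add one sentence: the primary analysis is an ANCOVA of T4 RMDQ on treatment arm with T2 RMDQ as covariate, reporting the adjusted mean difference with its 95% confidence interval. Fix this before unblinding. The unadjusted difference can be reported beside it as a supporting result.

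Optional additions, none of them needed for the correction:

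- Using T1 as well as T2 gains little. With r = 0.5 and an assumed T1–T2 correlation of 0.8, the variance ratio moves from 0.75 to 1 − 2·0.25/1.8 = 0.72.
- Sub-acute versus chronic status could be a second covariate.
- A repeated-measures model including T3 would use data from participants who leave before T4.

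The cost is one sentence. Every variable is already scheduled, and the sample size does not change. If the sponsor regards this as an important change to the method of analysis, the Protocol changes section already provides for submitting it to the ethics committee as an amendment.
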